#### Subgroup Outcome Analyses

Checks for the consistency of the intervention effects across sites will be done using a 2-way analysis of variance with the 2 factors being group (intervention/control) and site. Similarly, a subgroup analysis will be carried out according to the severity of cognitive impairment. These subgroups will be formed based on the MMSE score corrected by educational level and age.

#### Adjusted Analyses

A secondary analysis will be an analysis of covariance to compare the 18-month total QoL-AD score means, where the response variable will be the 18-month total QoL-AD score and the covariate will be the baseline total QoL-AD score. This analysis will provide a comparison of the 18-month total QoL-AD score means adjusted for the baseline total QoL-AD score. Again, the *P* value will be obtained using a Monte Carlo permutation method, and the 95% confidence limits for the adjusted difference between the means will be obtained using a bootstrap approach.

#### Procedures to Account for Missing or Spurious Data

For analyses involving multiple regression analysis, a multiple imputation approach will be considered and used, if statistically sound, depending on the proportion and pattern of missing values.

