### Sample Size

A total of 1200 dyads (PwMCI+carers) is the target for recruitment, divided over 2 groups: an intervention group, using the SMART4MD app, and a control group, not using the SMART4MD app. In this clinical trial, QoL is the primary outcome measure, measured by the QoL-AD total score [33]. This score is based on 13 four-point (1 to 4) items on a discrete visual analog scale. Recent papers [34] show the standard deviation (SD) of the total QoL-AD score approaches 7.

To detect a small effect size of 0.2 comparing 2 groups (intervention and control), using a 2-sided *t* test with a 5% statistical significance level, with a power of 80%, the minimum number of PwMCI required in each group is 394 (788 overall). If there would be a dropout rate of 20%, the number of PwMCI registered on the study would need to be 493 in each group (thus 986 overall).

On the other hand, one of our secondary objectives is to increase adherence to prescribed medication by 10% in the intervention group. If we consider that in people with dementia, the treatment adherence is between 44% and 99% [35,36], and assuming the less prevalence (44%), which we want to increase by 10%, with a power of 0.8 and a significance level of .05, we need 1174 subjects (20% dropouts included). Therefore, the sample size of this study is adequate to detect statistical and clinical differences between groups for the QoL-AD (primary outcome) and treatment adherence (a secondary outcome).

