#### Summary of Baseline Data and Persons With Mild Cognitive Impairment Progress Through the Trial

For continuous variables we will collect the mean, median, minima and maxima, lower and upper quartiles, and SD. Categorical variables will be summarized using counts and percentages. The progress of the PwMCI will be shown schematically with counts and percentages in a CONSORT diagram. The analysis will adopt the intention-to-treat principle.

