#### Primary Outcome Analysis

The primary analysis will be the comparison of total QoL-AD score mean changes (at 18 months) between intervention group and control group using a 2-sample, 2-sided Monte Carlo permutation *t* test. The use of a permutation test will avoid the need for strong assumptions about the distribution of the data. Similarly, a bootstrap approach will be used to obtain the 95% confidence limits for the difference between the group means.

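### The missing-data rule covers only regression analyses, so the primary test of 18-month QoL-AD change in effect uses only participants with an 18-month score and can be biased if dropout differs between arms

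*Protocol article*

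**What the plan says.** All of this is in the Protocol article.

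- **Primary Outcome Analysis:** "The primary analysis will be the comparison of total QoL-AD score mean changes (at 18 months) between intervention group and control group", by a two-sample, two-sided Monte Carlo permutation t test with bootstrap confidence limits. The reason given is that "The use of a permutation test will avoid the need for strong assumptions about the distribution of the data".
- **Procedures to Account for Missing or Spurious Data:** the section is a single sentence. "For analyses involving multiple regression analysis, a multiple imputation approach will be considered and used, if statistically sound", depending on how much is missing and in what pattern.
- **Summary of Baseline Data and Persons With Mild Cognitive Impairment Progress Through the Trial:** "The analysis will adopt the intention-to-treat principle".
- **Sample Size:** "If there would be a dropout rate of 20%, the number of PwMCI registered on the study would need to be 493 in each group". The target effect is 0.2 SD with an SD near 7.
- **Follow-Up Visits, Table 1:** QoL-AD is collected at baseline and at 6, 12 and 18 months. MMSE is collected at screening and at the same three follow-up visits.
- **Adjusted Analyses:** a secondary ANCOVA relates the 18-month score to the baseline score. It also needs the 18-month score.

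**The concern.** A change at 18 months exists only for someone who has both scores. The primary method is not a regression, and the missing-data section offers imputation for regression only. Taken together, these sections make the primary result a completer comparison, although no sentence says so. Enlarging the sample for dropout restores power but does nothing about who is left. The permutation test relaxes assumptions about the shape of the distribution, not about selection.

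The two arms are not asked to do the same thing. Only the intervention arm is expected to use a tablet app every day, and the authors themselves note that this age group is less familiar with digital devices. Different reasons for leaving, or different rates, are therefore plausible. The target effect is small, so modest selection could produce a false benefit or hide a real one. The QoL-AD scores collected along the way carry information on those who leave later, and the primary estimate does not use them.

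**Working it through.** **1. The plan's own figures.** Inputs from Sample Size: effect 0.2 SD, two-sided 5%, power 80%, dropout 20%.

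- Normal approximation: n = 2 × (1.960 + 0.842)² / 0.2² ≈ 392.4, so 393 per group. The exact t-test solution is 393.4, so 394, as stated.
- With dropout: 394 / 0.8 = 492.5, so 493 per group and 986 overall, as stated.
- Target in points: 0.2 × 7 = 1.4.

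The sample size for the primary outcome reproduces and is not the problem.

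**2. How many leave the primary test.** At the 1200 target with 20% dropout, 1200 × 0.8 = 960 have an 18-month score (480 per arm) and 240 do not. Power for 0.2 SD with 480 per arm is still about 87%. Any harm is therefore to validity, not power.

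**3. Bias of a completer comparison.** In one arm let d be the dropout share. Let g be the mean 18-month change in completers minus the mean that dropouts would have shown. The mean for the whole arm is (1 − d) × completer mean + d × dropout mean, so the completer mean exceeds it by d × g. For the contrast, intervention (I) minus control (C):

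bias = d_I × g_I − d_C × g_C

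**4. Type I error given that bias.** With no true effect and 600 randomised per arm:

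- SE = 7 × √(1/n_I + 1/n_C), where n = 600 × (1 − d)
- rejection rate = 1 − Φ(1.96 − bias/SE) + Φ(−1.96 − bias/SE)

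**5. Assumptions.** Dropout by arm and the gaps are not in the protocol and are assumed. The SD of 7 is stated for the total score; using it for the change is also an assumption (it holds if the baseline to 18-month correlation is 0.5). A smaller SD of change would leave the bias in points the same and raise the type I error.

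| Dropout I / C | Gap I / C (points) | Bias (points) | Share of 1.4 | Type I error |
|---|---|---|---|---|
| 20% / 20% | 3.5 / 3.5 | 0.20×3.5 − 0.20×3.5 = 0 | 0 | 5% |
| 20% / 20% | 3.5 / 0 | 0.20×3.5 = 0.70 | 50% | about 34% |
| 20% / 20% | 0 / 3.5 | −0.20×3.5 = −0.70 | −50% | about 34% |
| 25% / 15% | 3.5 / 3.5 | 0.25×3.5 − 0.15×3.5 = 0.35 | 25% | about 12% |
| 30% / 10% | 3.5 / 3.5 | 0.30×3.5 − 0.10×3.5 = 0.70 | 50% | about 34% |

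Worked case, row 2: SE = 7 × √(2/480) = 0.452; bias/SE = 0.70/0.452 = 1.55; 1 − Φ(0.41) ≈ 0.34, and the other tail is negligible.

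Worked case, row 4: n = 450 and 510; SE = 7 × √(1/450 + 1/510) = 0.453; bias/SE = 0.773; 1 − Φ(1.187) + Φ(−2.733) ≈ 0.118 + 0.003 = 0.121.

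**The case against.** The strongest reply is that handling of missing primary data usually belongs in the SAP, which is not shown, and that this is a condensed article. The missing-data sentence says what happens for multiple regression; it contains no word such as only, and nowhere is the primary analysis set in completers. This stands in part: the completer reading is an inference. But the article is not silent. It has a section on missing data, and the scope stated there leaves out the primary test. An SAP that followed the text would carry the gap forward.

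Several stronger readings are tempting, and the protocol does not support them.

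- **That the plan contradicts intention-to-treat.** The principle means first that people are analysed as randomised, and nothing here excludes non-users or moves anyone between arms. There is a tension, because the principle is left incomplete for those without an 18-month score, but no contradiction.
- **That 20% dropout is expected.** The sentence is conditional, a planning allowance.
- **That the test is valid only if data are missing completely at random.** For a comparison between arms this is too strict. Row 1 of the table has outcome-related dropout and no bias.
- **That the bias favours the app.** This needs selection to be stronger in the intervention arm; row 3 reverses the sign. Giving up the app is also not the same as leaving the trial, and nothing in the protocol ends follow-up when app use stops.
- **That using the intermediate visits would remove the bias.** They do so only if dropout depends on scores already observed. People who leave before month 6 have none, and dropout may depend on the unseen outcome.

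An 18-month endpoint is legitimate in itself, and leaving months 6 and 12 out of the contrast is not an error on its own. The ANCOVA, with group and baseline as regressors, might fall under the imputation rule; the text is unclear. It is secondary, so it relieves the primary analysis little.

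**Conclusion.** The point holds in a limited form, as a SHOULD-FIX. The missing-data rule as written does not cover the primary test, so the primary estimate would in effect rest on participants with an 18-month score.

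Bias is possible, not shown. It requires dropout to differ between arms in rate or in its relation to outcome, which the unequal demands on the arms make plausible. Within the assumed scenarios it runs from zero to 0.70 points in either direction, against a 1.4-point target, with type I error from 5% to about 34%. These figures rest on assumed dropout shares and gaps and on an SD of 7 for the change; they are illustrations, not forecasts.

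**What to change.** Extend the section on missing data to the primary outcome, before any outcome is compared by arm.

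- Estimate the 18-month contrast in all randomised PwMCI. The smaller change is multiple imputation by arm, using baseline, 6- and 12-month QoL-AD, MMSE and site. A repeated-measures mixed model over the four QoL-AD time points is an alternative.
- Keep the permutation t test in those with an 18-month score as a sensitivity analysis. This preserves the distribution-free check that the authors wanted.
- Add a delta-adjusted (tipping-point) analysis that shifts the imputed values, separately by arm, until the conclusion changes. It is needed because intermediate scores reduce but do not remove bias when dropout is early or depends on unobserved outcomes.
- State whether the imputation rule applies to the ANCOVA.

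The cost is a revised paragraph and some extra analysis work; no new visits or data are needed. The price in assumptions is that the main estimate then relies on data being missing at random given the recorded scores, which the delta-adjusted analysis is there to test.

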#### Methods to Ensure Validity and Quality of Data

Accurate and reliable data collection will be assured by verification and cross-check of the electronic case report form (eCRF) against the investigator´s records (source document verification). Source document verification will be conducted for 5% of data in subjects.

A comprehensive validation check program using front-end checks in the eCRF will verify these data. Discrepancies and queries will be generated accordingly in the eCRF for Web-based resolution by the investigator at the site. In addition, the eCRF data will be reviewed on an ongoing basis for medical and scientific plausibility.

### Ethical Considerations

This study will conform to the principles of the declaration of Helsinki. Ethical approval for this trial was granted by the regional ethical review boards at each participating site ensuring full compliance with all research and legislative regulations in the respective countries. The major ethical considerations for this study with respect to the group with PwMCI have been analyzed in depth (Multimedia Appendix 3).

The database used for the unidentified clinical data is located physically at Blekinge Institute of Technology and is used for several other clinical studies including the Swedish National Study of Aging and Care following all relevant protocols for data security and integrity. The code key containing the identifier are kept in a locked cupboard on a computer/Universal Serial Bus memory not connected to the internet.

## Results

Inclusion of participants started in December 2017, and recruitment is expected to end in February 2019. Furthermore, there will be 3 follow-up visits at 6, 12, and 18 months after the baseline visit.

## Discussion

The benefits of this RCT will be at several levels including in-depth knowledge of the possibilities of introducing a holistic multilayered ICT solution for this particular group. Support for the hypothesis that particular SMART4MD functions may improve QoL In PwMCI can be found in other studies. For example, SMART4MD enables users to record a list of their medication, to receive reminders to take their medication, and to record that they have done so. In this way, it encourages treatment adherence. An association between treatment adherence in Alzheimer disease and improved QoL for persons with dementia is claimed in a nonsystematic review of literature on factors affecting adherence to cholinesterase inhibitors, the main class of therapeutic drugs [35]. More specifically, 1 study [49] (the first to address this specific issue) found that people taking acetylcholinesterase inhibitors rated their QoL (using the total QoL-AD score) more highly than those who did not. Similarly, the control of dementia risk factors has consistent evidence for dementia prevention, especially in those at risk of developing dementia because of memory claims and/or MCI. Therefore, the adequate control of chronic diseases, such as hypertension, diabetes, and hypercholesteremia, for which an adequate adherence to pharmacological treatment is necessary, could imply an improvement in the QoL [50].

SMART4MD also enables users to access information about dementia and MCI. A systematic review of literature on information services for persons with dementia and informal carers [51] found that 2 out of the 3 RCTs measuring the QoL of the person with dementia under these circumstances indicated benefit. A systematic review of literature on social support group interventions for person with dementia identified 2 studies, 1 of which showed the QoL benefit of a support group providing educational seminars and supportive discussion on medical causes and treatments and future planning and strategies for enhancing communication and daily living [52,53].

The secondary objectives of the trial comprise establishing possible improvements in medication adherence, functional status, and informal carers’ well-being as a result of using SMART4MD.

The proposition that particular SMART4MD functions may promote these outcomes is also supported in literature. Reviews demonstrating that oral acetylcholinesterase inhibitors improve performance in activities of daily living [54,55] mean that the medication reminder function is well placed to support functional status. Other studies have shown that digital games can support communication and a sense of well-being in persons with dementia [56] and that multimedia memory aids can promote recall [57]. A recent systematic review has also shown some positive results for computerized cognitive training in population with MCI or dementia [58]. Providing information about dementia to informal carers as well as supporting them in mobilizing social support networks have been shown to reduce informal carers´ burden [59]. There is also a significant burden in informal caregivers of individuals with MCI [60]. Assistance with medication regimes not only has the capacity to improve QoL in person with dementia’s or MCI but also that of informal carers [61].

SMART4MD has been developed from an existing general health management app in a process involving the structured participation of PwMCI, their informal carers, and clinicians. The adoption of SMART4MD by older people faces the challenge of this age group’s relative unfamiliarity with digital devices and services. However, this challenge can also be seen as an opportunity. This research entails developing a digital device, which is specifically tailored to a group of people who are particularly at risk of digital exclusion. In this respect, the research responds to the wider call for the development of digital devices that are accessible and affordable to older people, rather than a source of anxiety [62].

SMART4MD’s combination of a number of functions distinguishes it from other comparable products and services, making it the kind of innovative nonpharmacological intervention that experts in the field have called for [56].

The occurrence of dementia and MCI is a common problem across Europe, but its management varies between countries and even regions. Variations in the commitment of member states to national dementia strategies naturally translates into variations in clinical practice through differences in both funding and priority given to dementia in different countries. More generally, health care systems vary widely between member states and regions, with differing emphasis placed on home, community, primary, and secondary care. These differences are further amplified by varying practice in reimbursement of health care costs between private health care insurers and public authorities; and by different levels of funding available for health care. As a result, the support and treatment available for PwMCI across the European Union varies widely. By including PwMCI, informal carers, and health care professionals from various European countries in this study, we can ascertain whether SMART4MD can support PwMCI and informal carers irrespective of these differences in services and treatments.

## Appendix

Multimedia Appendix 1 The intervention strategy for Support Monitoring and Reminder for Mild Dementia.

Multimedia Appendix 2 Support Monitoring and Reminder for Mild Dementia questions on experience of and familiarity with technology.

Multimedia Appendix 3 Additional brief clarification for the potential ethics issues associated with longer-term trials involving older persons with mild cognitive impairment.

## Abbreviations

ARCTU: Anglia Ruskin Clinical Trials Unit
CONSORT: Consolidated Standards of Reporting Trials
eCRF: electronic case report form
EQ-5D: EuroQoL-5D
GDS-15: Geriatric Depression Scale
ICTs: information and communication technologies
MCI: mild cognitive impairment
MMSE: Mini-Mental State Examination
PwMCI: persons with mild cognitive impairment
QoL: quality of life
RCT: randomized controlled trial
SMART4MD: Support Monitoring and Reminder for Mild Dementia
TAU: treatment as usual
ZBI-12: Zarit Caregiver Burden Interview
